### 2.12. Study Implementation

The 2–6-year-old children visiting the primary health care center (Amrita Kripa Health Care Centre) for routine dental/medical care or accompanying parents requiring dental/medical care will be invited to be a part of the study. On dental examination, if the child is found to satisfy the inclusion criteria, then the parent of the child will be given the option for treating the carious lesion by SDF treatment or by routine restoration. If the parent opts for SDF treatment for the child, then an option to participate in the trial will be given. If the parent agrees, then the consenting process is followed. Informed consent in the local language will be obtained from willing participants.

The selected child for trial will be randomly allocated to one of the three intervention arms as per computer-generated randomization sequence stratified at 40% type of tooth (anterior) and 50% gender. In this process, stratification is performed by gender (males, females) and type of primary tooth (anterior, posterior), so will have a total of 4 strata (2 by 2). Treatment assignments are then made from separate computer-generated randomization lists created in advance for each stratum. This randomization sequence will be generated from a remote site independent from the knowledge of the Principal Investigator (PI).

The randomization will be completed by a trial coordinator based on the computer-generated randomization sequence. The randomization list will remain with the trial coordinator until the completion of the study. The intervention (SDF application) will be performed by the PI and outcome assessment will be performed by two investigators other than the PI. Due to the obvious nature of the treatment neither the investigator performing the treatment, nor the study participant can be blinded. However, the outcome assessors are proposed to be blinded.

Allocation concealment will be conducted using opaque sealed envelopes (sealed sequentially numbered envelops irreversibly) containing codes (corresponding to the randomization list). The allocation concealment will be performed by one author (RV). The allocation sequence will not be disclosed to the PI until the completion of the study.

The study requirements, ensuring standardization in the assessment of the cavitated dental lesion, assessment of arrested lesion, application of the 38% SDF varnish to the child, counselling for adherence and eliciting of information from study participants in a uniform reproducible manner will be undertaken before the beginning of the trial at Amrita Kripa Health Care Centre. The data to be collected and the procedures to be conducted at each visit will be reinforced to all the personnel related to the trial. Entering data forms, responding to data discrepancy queries and general information about obtaining research quality data will also be covered during the training session. Calibration will be performed before and during the trial, and reliability expressed using Cohen’s kappa statistic. Once a child is enrolled or randomized, the study site (Amrita Kripa Health Care Centre) will make every reasonable effort to follow the child for the entire study period of 12 months.

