Tribal children face many health disparities compared with the mainland counterparts [32]. The prevalence of ECC is 74.7% in these tribal children compared to their counterparts [7]. The oral health disparities for these children exemplify, many of the inequities and early care services in these communities. SDF as a chemotherapeutic agent for prevention and managing of ECC would be a crunch point as it is a simple technique, acceptable, and cost-effective strategy over restorations and hospital-based management. The SDF effectiveness in these high-risk caries children will generate the evidence to use SDF as a caries preventive tool to the population having less access to regular dental care. The trial findings may also help in reducing pain, improving quality of life, and significantly reducing costs, all contributing to substantial reductions in disparities in caries the disparities in between access to preventive care. The use of SDF to prevent or delay surgical intervention until after the age of 3 years makes it a potentially attractive adjunctive therapy for managing caries in the young pediatric population.

Though the evidence is clear that the use of 38% SDF is effective for arresting dental caries, the determination of an optimal SDF application frequency for a cavitated lesion in pragmatic settings is important especially among high caries risk tribal children who have poor access to oral care. Thus, the primary objective of this trial is to compare the effectiveness of an annual, semi-annual, and four times a year application of 38% Silver Diammine Fluoride in arresting active coronal carious lesions on primary teeth of tribal preschool children in India. The secondary objective is to assess the acceptability of SDF treatment by the child as well as parent/s.

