### 2.5. Eligibility Criteria

#### 2.5.1. Inclusion Criteria

Children of any gender aged 2–6 years with the presence of cavitated caries lesion classified as stage 5–6 following the Modified International Caries Detection and Assessment System (ICDAS).The parent of the child understands the importance of SDF treatment to arrest prevent dental caries.Parent of a child willing to accompany the child at required intervals for evaluation.

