#### 2.5.2. Exclusion Criteria

Children with ulcerative gingivitis or stomatitis.Developmental dental abnormalities such as enamel defects.Serious chronic medical conditions, such as congenital heart disease.Cavitated teeth that are nearing natural exfoliation time.Children with more than one-third of the crown missing, or pulpal involved (tooth with pulp exposure, presence of an abscess or a sinus, obvious discoloration, and premature hypermobility were regarded as pulpal involved tooth)Known silver allergy.Uncooperative children (after the failure of basic pediatric patient management protocols)Children with special health care needs.

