### 2.9. Secondary Outcome

To assess the children (and/or parents) satisfaction and acceptability and dentist factors associated with the use of the SDF. This will be assessed with the help of a self-reported questionnaire.

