### 2.14. Adverse Events

The 38% SDF used in this trial is employed in routine clinical practice as a standard of care procedure. The potential risks for a child are minimal and identical to the risk for children obtaining routine dental care. The only foreseeable risk would be an allergic reaction to SDF. Silver diamine fluoride stains clinic surfaces and clothes. At each contact with the study participant, investigators will seek information on adverse events by specific questions and an oral examination.

The child may experience a transient metallic or bitter taste. Even a small amount of silver diammine fluoride can cause a “temporary tattoo” to the skin (on the patient or dentist). The patient will be informed about the same during the consenting process and reinforced during the follow-up visits. If the child/parent refuses to participate at any point in time owing to any of the above-mentioned conditions, he/she will be considered as a drop-out. Stain on the skin resolves with the natural exfoliation of the skin, usually in 2–14 days. Universal precautions will prevent most exposures to the adjacent tissues. Isolation of the areas to be treated with cotton rolls and application cocoa butter to protect surrounding gingival tissues will prevent inadvertent exposure. Spills can be cleaned up immediately with copious water, ethanol, or bleach. High pH solvents such as ammonia may also be used. Secondary containers and plastic liners for surfaces are adequate preventives.

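### The acceptability outcome describes only families who had already chosen SDF, and refusals over taste, staining or reaction become drop-outs without counting against it

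*Protocol article*

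**What the plan says.** The Introduction of the protocol article states: "The secondary objective is to assess the acceptability of SDF treatment by the child as well as parent/s". Section 2.9 names satisfaction and acceptability as the secondary outcome and adds: "This will be assessed with the help of a self-reported questionnaire". Neither section 2.9 nor Table 1 gives a time point for the questionnaire.

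Entry is described in section 2.12. After a qualifying examination, "the parent of the child will be given the option for treating the carious lesion by SDF treatment or by routine restoration". Then: "If the parent opts for SDF treatment for the child, then an option to participate in the trial will be given". Section 2.5.1 also lists as an inclusion criterion that "The parent of the child understands the importance of SDF treatment", and section 2.5.2 excludes children who remain uncooperative after basic behaviour management.

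Section 2.14 names allergic reaction, a passing metallic or bitter taste, and staining of skin, clothes and clinic surfaces. A child or parent who refuses to go on "owing to any of the above-mentioned conditions, he/she will be considered as a drop-out". Section 5 says that drop-outs after six months are included, with imputation, and that reasons for withdrawal are assessed in each group and reported qualitatively.

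**The concern.** Two features of the plan affect what the acceptability result can mean.

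- **Entry.** A parent who prefers restoration to SDF gives direct information about acceptability at this clinic, but never enters the trial. The stated objective carries no such restriction. The Introduction speaks of evidence for a population with little access to dental care, and section 7 plans recommendations to local health authorities. A reader could take the result as acceptability among tribal families in general.
- **After entry.** Refusing to continue because of taste, staining or a reaction is the clearest sign of non-acceptance that the trial can observe. The plan codes it as a drop-out and does not say that it counts against acceptability.

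At stake is the reading of a secondary outcome. The primary caries-arrest result is not affected by this point.

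**Working it through.** The plan gives no target, rate or power for acceptability, so there is no stated figure to reproduce. The sample size in section 2.11 concerns caries arrest only. The calculations below are illustrations.

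**Inputs from the protocol article**
- 160 children per arm and about 30% expected loss (section 2.11): 160 × 0.70 = 112 remain and 48 are lost.
- Applications: arm 1 has one (baseline); arm 2 has two (baseline, 6 months); arm 3 has four (baseline, weeks 2, 4 and 8) (section 2.7, Table 1).

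**Assumed inputs, not in the documents**
- Share of parents choosing SDF, s: 0.5 to 0.9.
- Acceptability among choosers, A1, and among those observed in the trial, A: 0.90.
- Acceptability among those choosing restoration, A0: 0 to 0.5.
- Share of drop-outs who are refusers, f: 0 to 1.
- Refusal risk per repeat application, r: 3% to 10%.

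**1. Entry filter.** Acceptability among all eligible families = s × A1 + (1 − s) × A0.
- s = 0.5: 0.45 + 0.50 × (0 to 0.5) = 45% to 70%.
- s = 0.7: 0.63 + 0.30 × (0 to 0.5) = 63% to 78%.
- s = 0.9: 0.81 + 0.10 × (0 to 0.5) = 81% to 86%.

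Against 90% observed, the gap is 4 to 27 points for s between 0.7 and 0.9, and 20 to 45 points for s = 0.5. The filter acts before randomisation, so it is the same for all three arms.

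**2. Refusals coded as drop-outs.** Count refusers as not accepting, and let other drop-outs have the same acceptability as those observed. Then the all-randomised figure = (1 − d) × A + d × (1 − f) × A = A × (1 − d × f), with d = 0.30.
- f = 0: 0.90 × 1 = 90%.
- f = 0.25: 0.90 × 0.925 = 83%.
- f = 0.50: 0.90 × 0.85 = 76.5%.
- f = 1: 0.90 × 0.70 = 63%.

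The gap is 0 to 27 points.

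**3. Differences between arms.** With k applications there are k − 1 repeat applications, so the share refusing at least once = 1 − (1 − r)^(k − 1). For k = 1, 2 and 4:
- r = 3%: 0%, 3%, 9%.
- r = 5%: 0%, 5%, 14%.
- r = 10%: 0%, 10%, 27%.

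Arm 3's repeat applications all fall by week 8, before the six-month point. Arm 2's single repeat falls at that point, and arm 1 has none. A refusal prompted by a repeat application in arm 3 during its schedule therefore lies in the period for which section 5 does not state that drop-outs are included.

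**The case against.** The other side has a good deal to say.

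- **Selecting willing families is inherent in this design.** Every arm receives SDF, so only families willing to have it can be randomised. The restriction is equal across arms and cannot bias one against another. This stands. What remains is that the objective is worded without the restriction.
- **The two eligibility criteria are weak evidence.** Understanding the importance of SDF is comprehension, not approval, and excluding uncooperative children is about feasibility. This stands; the point rests on the SDF-or-restoration choice.
- **Refusers may still be asked.** The questionnaire has no stated time point, and nothing says that drop-outs go unasked. Section 2.13 ties the six-month point to the first outcome assessment, which is caries arrest, so applying that rule to the questionnaire is an inference. This stands. Even so, no passage says that a refusal counts as non-acceptance.
- **Withdrawal reasons are collected by group.** Section 5 provides for this, and section 2.14 seeks adverse events at each contact, so such refusals would be visible by arm. This stands, but they are reported only qualitatively and do not enter the outcome.
- **No between-arm comparison of acceptability is stated.** This also stands. Unequal refusal by arm would matter only if results are shown or compared by arm.
- **The magnitudes are assumed.** Section 2.11 attributes the expected loss to the population and the demands of repeated follow-up, not to taste or staining. The staining named in section 2.14 is not of teeth.

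**Conclusion.** The concern holds in a limited form. The questionnaire can describe acceptability only among families who chose SDF, which limits the absolute level and its generalisability. In addition, the stated coding gives refusals over taste, staining or reaction no weight in the acceptability outcome.

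The size is not fixed by the documents. Under the stated assumptions, the entry filter overstates acceptability among all eligible families by 4 to 27 points when 70% to 90% of parents choose SDF. The drop-out coding overstates it by 0 to 27 points at 30% loss. The direction rests on decliners being no more accepting than choosers, and on refusers counting as non-accepting. The second effect is nil if no drop-outs are refusers.

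A reader might infer more, but the documents do not support it:
- that the acceptability figure must come out high: the drop-out effect may be zero;
- that the entry route biases the arms against each other: it acts equally on all three;
- that refusers certainly leave the acceptability data: the questionnaire's timing is not given;
- that acceptability among all those offered SDF equals uptake multiplied by the trial's figure: this sets acceptability among parents choosing restoration to zero, whereas preferring one option does not make the other unacceptable.

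This is a cheap improvement to a secondary outcome.

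**What to change.** 1. Score any refusal or withdrawal attributed to taste, staining or reaction as not acceptable in the child's randomised arm, whenever it occurs. The withdrawal reasons already planned in section 5 supply the data.
2. State the acceptability conclusion as applying to families who chose SDF.
3. At the offer in section 2.12, record how many eligible parents were given the choice, how many chose SDF and how many chose restoration. Report these counts as a descriptive companion to the questionnaire. They should not replace it, because uptake before treatment and experience after treatment are different things.

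The cost is a small screening tally, a scoring rule and a possibly lower reported acceptability figure. Treatment, randomisation and the primary analysis do not change. The tally needs to be kept at screening, since choices not recorded then may not be recoverable.

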### 2.7. Interventions

#### Silver Diammine Fluoride

SDF is a colorless liquid containing silver ionic particles. It contains 38% (44,800 ppm) fluoride ion at a pH of 10. This formulation constitutes 25% silver, 8% ammonia, 5% fluoride, and 62% water. One drop (0.05 mL) of 38% SDF solution (2.24 F-ion mg/dose) is required for the treatment of one tooth. The SDF treatment protocol consists of removing gross debris from the cavitated tooth, drying the affected area, isolating the tooth with the help of cotton rolls and suction, placing a small amount of SDF on the affected area, gently drying the SDF for 1 min, removing excess SDF with cotton gauze and isolating the tooth for up to 3 min [34]. This procedure will be performed after the tooth is removed of debris (with the aid of a toothbrush) and soft caries using a spoon excavator. It includes gross debris from cavitation to allow better SDF contact with denatured dentin. Carious dentin excavation before SDF application is not necessary. As excavation may reduce the proportion of arrested caries lesions that become black, it may be considered for esthetic purposes. No rotary instruments will be used for caries removal.

The study participants will be allocated into one of the three parallel arms who will receive 38% SDF application as follows:
Study arm 1: annually (once a year; baseline visit);Study arm 2: bi-annually (twice a year at 6-month intervals; baseline visit and after 6 months);Study arm 3: four times a year (baseline visit, 2nd, 4th, and 8th week).

In the baseline visit in all the study arms, the child will be assessed for cavitated caries lesions and caries risk (ADA Caries Risk Assessment Form (Age 0–6)). After obtaining consent for the trial, SDF is applied on the selected caries teeth depending on the study arm. The demographic characteristics, plaque index, and caries status will be assessed. In the subsequent visits depending on the study arm, SDF will be applied (Table 1).

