## Figures and Tables

**Figure 1 mps-04-00030-f001:**
[figure not shown]
Study flow diagram.

**Table 1 mps-04-00030-t001:** Participation timeline of the trial.

Procedures		Timeline					
		Visit 1	2	3	4	5	6
		Baseline	2 Weeks	4 Weeks	8 Weeks	6 Months	12 Months
Pre-screening consent		Yes	-	-	-	-	-
Eligibility assessment		Yes	-	-	-	-	-
Oral examination		Yes	Yes	Yes	Yes	Yes	Yes
Informed consent		Yes	-	-	-	-	-
Allocation to study arms		Yes	-	-	-	-	-
Caries Excavation		Yes					
Application of 38% SDF	Group 1	Yes	No	No	No	No	No
	Group 2	Yes	No	No	No	Yes	No
	Group 3	Yes	Yes	Yes	Yes	No	No
Outcome assessment		Yes *	-	-	-	Yes	Yes
Adverse event assessments		Yes	Yes	Yes	Yes	Yes	Yes

* Baseline assessment.

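### Section 2.12 rules out blinding of operator and family and sets no time of disclosure, although the baseline application is the same in all arms and annual and bi-annual do not differ until 6 months

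*Protocol article*

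**What the plan says.** **Blinding (Section 2.12).** On operator and family the article says: "Due to the obvious nature of the treatment neither the investigator performing the treatment, nor the study participant can be blinded". No time point is attached. On assessment it says: "However, the outcome assessors are proposed to be blinded". The roles are separated: "The intervention (SDF application) will be performed by the PI and outcome assessment will be performed by two investigators other than the PI".

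**Concealment (Section 2.12).** "Allocation concealment will be conducted using opaque sealed envelopes", sequentially numbered and holding codes that correspond to the list. The trial coordinator keeps the list. No time of opening is given. The section closes with: "The allocation sequence will not be disclosed to the PI until the completion of the study".

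**Treatment at visit 1 (Section 2.7 and Table 1).** After consent, "SDF is applied on the selected caries teeth depending on the study arm". Table 1 marks the row "Allocation to study arms" at visit 1 only. The same table marks an SDF application at baseline for all three groups.

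**The concern.** In a trial of application frequency, the treatment reveals the arm only once the schedules diverge. Here that is later than the blinding statement implies, so the reason given for not blinding does not cover the whole trial.

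What is at stake is the baseline visit. The operator selects the teeth, removes debris and soft caries, dries, applies and isolates. Section 2.7 calls for removal of soft caries but also describes excavation of carious dentin as unnecessary and optional. Those statements need reconciling, and as they stand they leave room for judgement. The lesions treated at this visit are the denominator of the primary outcome (Sections 2.8 and 4). The baseline application is the only exposure in arm 1 and one of two in arm 2. An operator who knows that a child will not be treated again, or will be treated three more times, may select or prepare lesions differently. Blinded assessors at 6 and 12 months cannot undo that.

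A second route is retention. A family that knows no further treatment is planned has a different reason to return at 6 months from one that expects a second application. Section 2.11 allows for about 30% loss to follow-up. Section 2.13 withdraws children who miss two rescheduled appointments and keeps person-time for those who complete six months.

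**Working it through.** **Step 1. Compare the schedules (Section 2.7; Table 1).**

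| Visit | Arm 1 | Arm 2 | Arm 3 |
|---|---|---|---|
| Baseline | SDF | SDF | SDF |
| 2, 4, 8 weeks | none | none | SDF |
| 6 months | none | SDF | none |
| 12 months | none | none | none |

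First visit at which the applications differ:
- arm 1 versus arm 2: 6 months
- arm 3 versus arm 1, and arm 3 versus arm 2: week 2
- no pair differs at baseline

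Section 2.10 says the number of visits depends on the arm, while Table 1 lists an oral examination at all six visits without splitting by arm. On either reading, nothing in the table separates arm 1 from arm 2 before 6 months.

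**Step 2. Set this against Section 2.12.** The baseline application can be completed in all 3 × 160 = 480 children without anyone present knowing the arm. Annual versus bi-annual can stay undisclosed in 2 × 160 = 320 children until the 6-month outcome is recorded. Arm 3 must be known by the end of visit 1 so that week 2 can be booked, or at the latest at week 2. The statement that operator and participant cannot be blinded is right for the 12 months as a whole, but wrong for these two periods.

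**Step 3. Illustrate the size.** The plan has no figure to reproduce here, and every bias input below is an assumption.

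(a) *Operator effect at baseline.* Inputs: 120 per arm (Section 2.11, before the allowance for loss); arrest rate 50% (assumed); outcome treated as one binary result per child (a simplification).
- SE of a difference = √(2 × 0.25 / 120) = 0.0645.
- Spurious shift of 0.05: 0.05 / 0.0645 = 0.775. P(|Z + 0.775| > 1.96) = 0.118 + 0.003 ≈ 0.12.
- Spurious shift of 0.02: 0.02 / 0.0645 = 0.31. The same formula gives about 0.06.

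(b) *Differential return, arm 1 versus arm 2.* If lost children have arrest lower by g than retained children, the mean among retained children exceeds the overall mean by g × loss. The bias in the contrast is then g × (difference in loss). With a loss difference of 0.10 and g from 0.20 to 0.40 (both assumed), it is 0.20 × 0.10 = 0.02 to 0.40 × 0.10 = 0.04, or 2 to 4 points. For scale, the largest difference the plan expects between two frequencies is 14% (Section 2.11).

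**The case against.** **The time of opening is operational detail that an article may leave out.** That is fair for the omission taken alone. It does not cover a positive statement, with a reason attached, that the article's own schedule contradicts for the baseline visit and for arm 1 versus arm 2 up to 6 months.

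**The sentence is true of the trial as a whole, and the design is defensible.** Both hold. Frequency is the intervention, the assessors are separate and proposed to be blinded, and the endpoint is hardness on probing. Application is scripted and standardised before the trial (Sections 2.7 and 2.12). These features limit bias, but they do not remove the operator's discretion at baseline.

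**Stronger readings that a reader might infer.** The documents do not support these:
- *That Section 2.12 reveals the arm at visit 1.* It does not say so. Allocation is placed at visit 1 and Section 2.7 makes the baseline application depend on the arm, which implies early knowledge without stating it.
- *That Table 1 places allocation before treatment because its row is higher.* The rows are not an order within the visit: the baseline assessment is listed below the application it must precede.
- *That the non-disclosure sentence about the PI cannot hold.* It speaks of the sequence, and the list stays with the coordinator. The natural reading is that the PI never sees the list but learns each child's arm by treating. It needs clarifying and is not a contradiction.
- *That all of this bias is avoidable.* Arm 3 is known from the end of visit 1, so differential return and leakage to assessors remain for the contrast that Section 4 tests, four times a year against the other frequencies.
- *That the plan expects annual and semi-annual to differ by under 10 points.* In Section 2.11 that figure follows the description of a cited study; the plan's own figure is 14%.
- *That children lost early certainly leave the analysis.* Sections 2.13 and 5 point that way, but Section 4 also names an intention-to-treat set of all patients as randomized.

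The direction of the operator effect is also unknown. Extra care for children treated only once would work against the superiority claim.

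**Conclusion.** The point holds in limited form. The statement that operator and participant cannot be blinded is broader than the schedule supports, the time of disclosure is not fixed, and Section 2.7 implies that the arm is known when baseline teeth are treated. Later disclosure would protect lesion selection and baseline technique in all three arms. It would protect retention to 6 months for annual versus bi-annual only. It leaves arm 3 open after visit 1.

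The size is not known. Error rates of about 6% to 12%, or a bias of 2 to 4 points in annual versus bi-annual, follow only from the assumed shifts, losses and arrest gaps. The retention figure also requires that children lost early are left out of the analysis. The case for change rests on the very low cost of the remedy, not on a demonstrated bias.

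**What to change.** Keep the lists, the 1:1:1 ratio and every application schedule as they are. Change only when the arm is disclosed.

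1. Record eligibility, the chart of lesions to be treated and the completed baseline SDF application. Only then open the child's numbered envelope, which shows arm 3 or arms 1/2 and no more.
2. For arms 1 and 2, hold a second sealed insert with the same number. Open it at the 6-month visit after the blinded assessor has recorded the outcome.
3. Restate the blinding sentence in Section 2.12: operator and family do not know the arm during the baseline application, nor arm 1 versus arm 2 until the 6-month outcome is recorded; after that they are open.
4. Reword Section 2.7 so that the baseline application no longer depends on the arm.
5. Clarify that the PI never sees the randomization list and learns individual assignments only at steps 1 and 2.

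The cost is a wording change and a two-part envelope, with no added visits or children. The one drawback is that parents must be told at consent that, if the child is in arm 1 or 2, they will learn at 6 months whether a second application is due. Both arms attend that visit in any case.
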